## Objectives

The main purpose of this study is to investigate the effect of different cushioning solutions on injury risk in leisure-time running. The project focuses on the influence of cushioning properties at the rear and the forepart of the running shoes on musculoskeletal problems in leisure-time runners. The primary objective of this study is to determine whether ‘extra soft’ cushioning material (ie, global stiffness: 40±5 N/mm) at the rear part of the shoe reduces injury risk compared with stiffer material (ie, global stiffness: 60±5 N/mm) in leisure-time runners. The secondary objectives of this study are to investigate whether (1) cushioning under the forepart of the shoe also influences injury risk, independently of the cushioning at the rear part, (2) the effects of cushioning properties and position on injury risk depend on the runner’s body mass and (3) perception of cushioning is related to both shoe cushioning and injury risk. The present study will also explore (1) if other weight-bearing locomotion activities (ie, number of steps per day in addition to the steps from running) represent an independent risk factor for running-related injury, (2) the role of (biological) sex in injury mechanism, as previous work showed that injury risk and risk factors may be different in men and women,^25^ and its potential moderation effect, (3) how acute changes in training load affect injury risk and (4) if disparities in injury risk exist according to the socioeconomical status of the runners (eg, level of education, socioprofessional category, gross annual household income).

Our main hypothesis is that greater shock absorption properties at the rear part of standard running shoes are associated with lower injury risk in recreational runners. Our secondary hypotheses are (1) greater shock absorption properties under the forepart of the shoe are also associated with lower injury risk in recreational runners, (2) runners with low body mass experience a lower injury risk in shoes with greater shock absorption properties,^17^ and (3) greater perceived cushioning is related to lower injury risk.

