### Sample size

A sample size calculation for Cox regression was used to determine the number of participants needed for the study’s primary hypothesis. With an alpha of 0.05 and a power of 80%, an average injury rate of 30%,^28 29^ an expected HR=1.50 between groups, 33% of participants randomised to each shoe group and an expected drop-out rate of 10%, the total number of participants required is 1068 (ie, 356 participants per group).

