### Statistics

Descriptive statistics will be presented as mean and SD for normally distributed continuous variables, median and range for skewed continuous variables, and count and percentage for categorical data, respectively. Shock absorption properties of the three shoe versions will be compared using an analysis of variance while considering the measurement uncertainty of the mechanical test.

Injury incidence will be computed for each outcome as the number of injuries per 1000 hours of running exposure. Injury prevalence will be computed for each outcome and per week by dividing the number of participants who reported an injury by the number of respondents of that week. Average weekly prevalence will be calculated separately for each outcome for the main anatomic locations.

To investigate the effect of shoe version, body mass and other possible risk factors on injury risk, subdistribution HR (sHR) with 95% CIs for the event of interest will be calculated using Fine-Gray models to account for competing risk. The date of inclusion and date of injury or censoring will be basic data used to calculate the time at risk, expressed in hours spent running and defined as the time scale.^14^ Participants will be right-censored if lost to follow-up or at the end of the intervention period. Average running practice characteristics will be computed for each participant over their specific period of observation. The assumption of proportional hazards will be evaluated using log-minus-log plots and Schoenfeld’s global test. First, unadjusted sHR will be estimated for shoe versions, body mass and other potential risk factors, such as running training characteristics. Subsequently, the variables with a p value <0.200 and well-established potential confounders will be included in an adjusted model to determine whether the model is improved with further adjustment. The model that best fits will be determined based on the log-likelihoods. Stratified analyses will be performed to investigate if the effect of shoe cushioning on injury risk is modified by sex, body mass (using the median value of body mass as cut-off, independently in men and women) or Body Mass Index. Finally, mediation analysis will investigate if the effect of cushioning on injury risk is partially explained by cushioning perception (and comfort).

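### Whether cushioning effects depend on body mass is to be investigated by separate stratified analyses, with no comparison between strata stated; a difference in significance between strata would not show modification.

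*Protocol article*

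**What the plan says.** The Objectives section makes dependence of the cushioning effect on body mass secondary objective 2. The matching hypothesis is that "runners with low body mass experience a lower injury risk in shoes with greater shock absorption properties". The role of sex, including as a moderator, is listed there among the exploratory aims.

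The Statistics section gives one method for these questions: "Stratified analyses will be performed to investigate if the effect of shoe cushioning on injury risk is modified by sex, body mass" or Body Mass Index. For body mass the strata are formed by "using the median value of body mass as cut-off, independently in men and women". The article nowhere states an interaction term, a ratio of subdistribution hazard ratios (sHRs) or any other comparison of one stratum with another.

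The Sample size section covers the primary hypothesis only: "With an alpha of 0.05 and a power of 80"%, "an average injury rate of 30"%, "an expected HR=1.50 between groups", with "33% of participants randomised to each shoe group and an expected drop-out rate of 10"%.

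**The concern.** Fitting the shoe effect separately in light and heavy runners answers two questions, one per half. It does not answer whether the halves differ. A significant result in one half beside a non-significant result in the other is weak evidence of a difference, because each half holds only half the events and about half the power.

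Two places in the article make this more than a formality. The Introduction reports that, in the same group's previous study, the benefit of more cushioning was confined to lighter runners, and it takes this as confirmation that weight moderates the effect. Also, the hypothesis is worded as a statement about light runners alone, so an identical benefit at every body mass would satisfy it.

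At stake is the reading of a named secondary objective. A trial in which cushioning works equally well for everyone could be reported as showing that it works only for light, or only for heavy, runners.

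**Working it through.** **Inputs.** HR 1.50, alpha 0.05, power 80%, injury rate 30%, drop-out 10% and 356 per group (Sample size); the main comparison is mixed versus hard (Intervention); about 40% women (Stratified randomisation). Alpha is taken as two-sided, since one-sided alpha gives a total of only 840.

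**1. The plan's own figure.** Schoenfeld's formula for two equal arms: events = 4 × (1.96 + 0.842)² / (ln 1.5)² = 191. Then 191 / 0.30 = 637, and 637 / 0.90 = 708, or 354 per group and 3 × 354 = 1062 in total. The stated total is 1068, so the figure is reproduced to within 1%.

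**2. Events per half.** Mixed versus hard has 2 × 356 = 712 runners. 712 × 0.90 × 0.30 = 192.2 events, or about 96.1 in each body-mass half if events split evenly.

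**3. Power per half, same HR of 1.50 in both.** Φ(√(96.1/4) × ln 1.5 − 1.96) = Φ(0.028) = 0.511.

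**4. Pattern of results, p = 0.511 in each independent half.**
- Both significant: p² = 26%.
- Neither: (1 − p)² = 24%.
- Exactly one, either one: 2p(1 − p) = 50%.
- Light only: p(1 − p) = 25%. Heavy only: 25%.

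Among simulated trials with a significant overall result, exactly one half was significant in 57% and only the light half in about 29%.

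**5. Range over the uniform true HR** (96 events per half, significance in the direction of benefit).

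| True HR in both halves | Power per half | Exactly one significant | Light only |
|---|---|---|---|
| 1.0 | 2.5% | 5% | 2% |
| 1.2 | 14% | 25% | 12% |
| 1.3 | 25% | 38% | 19% |
| 1.5 | 51% | 50% | 25% |
| 1.8 | 82% | 29% | 15% |
| 2.0 | 92% | 14% | 7% |

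If drop-outs cost no events (712 × 0.30 = 213.6), the HR 1.50 figures barely move: 49% and 25%.

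**6. Sex strata.** With events split 40/60 and a uniform HR of 1.50, power is 43% in women and 59% in men. Exactly one sex is significant in 0.43 × 0.41 + 0.59 × 0.57 = 51% of trials.

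**7. An interaction test instead.** At the 0.05 level it declares modification falsely in 5% of trials when the effect is uniform. The joint pattern of light significant, heavy not and interaction significant occurs in about 2.4%. For the median split, SE of the difference in log HR = √(4/96.1 + 4/96.1) = 0.288. Power is Φ(ln 1.5/0.288 − 1.96) = 29% for a ratio of HRs of 1.5, and 67% for a ratio of 2.0. It reaches 80% at exp(2.80 × 0.288) = 2.24.

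**The case against.** The article does not say that modification will be declared when one stratum is significant and the other is not. It plans sHRs with 95% CIs, which a careful reader can compare. The analysis plan and full protocol are not shown, and a product term could be specified there. The Introduction's remark on the previous study does not settle the matter either, since that study's own analysis cannot be seen.

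Much of this stands as a limit on the claim. The percentages above are conditional on judging strata by their own significance, a rule that the article's wording invites but does not state. What does not stand is that the matter is only omitted detail: the article names a method and a cut-off for this question, and that method does not test it.

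Three stronger readings are tempting and are not supported.
- A reader might infer that a finding of benefit in light runners only would arise by chance half the time. The 50% is for exactly one half, whichever it is. For equal independent halves p(1 − p) cannot exceed 25%, and HR 1.50 is where it peaks. Nor is it a false-positive rate under no shoe effect, which is about 2%.
- A reader might infer that the cut-off itself is wrong. A sample median is a rule fixed in advance, and taking it within sex keeps body mass from standing in for sex, in line with the stratified randomisation. A continuous analysis uses more of the information, but the choice of cut is largely preference.
- A reader might infer that the main result is at risk. The mixed-versus-hard test does not depend on these strata.

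**Conclusion.** The point holds with moderate severity. The stated method for secondary objective 2 does not test whether the effect depends on body mass, and the same applies to the looks by sex and Body Mass Index, with less weight there. Under the planned event count and a uniform HR of 1.50, judging by significance within halves would give a split verdict in about 50% of trials and light only in about 25%. The figures rest on equal events per half, independent halves, the planning assumptions for injury rate and drop-out, and a Cox/Schoenfeld approximation to what will be a Fine-Gray analysis. They move with the true HR as tabulated. They concern mixed versus hard only.

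**What to change.** State that secondary hypothesis 2 is tested by a shoe-by-body-mass interaction in the full-sample Fine-Gray model, with body mass continuous and sex in the model. Report the interaction estimate (ratio of sHRs) with its 95% CI and p value. As there are three shoe versions, say which contrast carries the test. Handle sex and Body Mass Index in the same way, labelled exploratory, and keep the median-split results as description only. If the full protocol or analysis plan already specifies this, the article's wording need only be aligned with it.

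The cost is one interaction per modifier in a model already planned, with no extra data, and it can be fixed before the shoe code is broken. The real downside is power: a median-split interaction has about 29% for a ratio of HRs of 1.5 and reaches 80% only near 2.24. A continuous term may do somewhat better, but the result may well be inconclusive. The plan should say so, and that a non-significant interaction will not be read as proof of equal effects.

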### Data collection

Participants must fill in a baseline questionnaire to collect information regarding sociodemographic characteristics, running experience, training habits, running competitions performed and injury history. The intervention period will start as soon as the participants receive their study shoes and will last 6 months. During this intervention period, the participants are required to use the study shoes for all their running activities, to continue their usual training or follow their planned schedule and to fill out the weekly questionnaire on musculoskeletal problems, as well as on the use of the study shoes during the follow-up. Data on running practice will be downloaded from sports watches and their respective app via Strava in our dedicated electronic system. The system will collect the daily step count via Google Fit and the Apple Health mobile app. Information on using the study shoes will be collected via a weekly questionnaire. Data on cushioning perception will be collected three times using a dedicated questionnaire distributed when the runner has cumulated 5 hours and 25 hours of running and at the end of the intervention, respectively (online supplemental material 3).

Participants will be asked to complete a weekly questionnaire on any problem in the lower limbs or lower back region experienced during the previous 7 days (the Oslo Sports Trauma Research Centre (OSTRC) Overuse Injury Questionnaire).^27^ On top of the four basic questions, information regarding the following is required: date of symptom onset, sports discipline, anatomical location, type of injury, recurrence (ie, new, recurrent, exacerbation or subsequent injury), mode of onset and estimated return date to full participation (online supplemental material 4). Individual e-mail reminders will be sent to the participants who do not complete a weekly questionnaire. Personal phone calls will be made to participants who do not react to the e-mail reminders and if the reported information in the injury form is inconsistent. Study participation will be terminated, and the participant will be right-censored if he/she does not fill in the weekly injury form for two consecutive weeks, does not reply (or react) to the automatic reminders and cannot be reached by phone by the research team.

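### Cushioning perception is first rated at 5 hours of running while risk time starts at inclusion, so in the mediation and perception–injury analyses the mediator can follow the injury

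*Protocol article*

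**What the plan says.** The Statistics section plans Fine-Gray models with time at risk measured in running hours. It runs from inclusion to injury or censoring, and censoring falls at loss to follow-up or at the end of the 6-month intervention. The same section then states that "mediation analysis will investigate if the effect of cushioning on injury risk is partially explained by cushioning perception (and comfort"). It does not name a measurement time for the mediator.

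Under Data collection, the perception questionnaire is "distributed when the runner has cumulated 5 hours and 25 hours of running and at the end of the intervention". No earlier perception rating is described.

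Under Study outcomes, the primary outcome is the first running-related injury during follow-up that restricts or stops running for at least 7 days. Under Objectives, the relation of perceived cushioning to injury risk is the third secondary objective, and the third secondary hypothesis is that greater perceived cushioning goes with lower injury risk. The Introduction adds that changes in perception and comfort might inform on injury risk.

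**The concern.** A mediator has to come before the event that it is meant to explain, and a predictor has to be known at the start of the risk time to which it is applied. Here every perception score arises after the clock has started. Two errors become possible.

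- **Reverse order.** A runner who is already injured may rate the shoe worse because of pain. That alone would produce the hypothesised link between greater perceived cushioning and lower injury risk.
- **Selection.** If only scores given before injury are kept, but risk time still starts at inclusion, scored runners are injury-free by construction up to the rating. That is immortal time, and it depends on the outcome.

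Randomisation of the shoe protects against neither, because perception is not randomised and is observed only after allocation. A positive result for mediation or for secondary hypothesis 3 could then not be interpreted.

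**Working it through.** **1. The plan's own figure.** Inputs from the Sample size section: alpha 0.05 (two-sided is my assumption), power 80%, 30% injured, HR 1.50, equal thirds, 10% drop-out.

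- Events for two groups (Schoenfeld): (1.960 + 0.842)² / (0.25 × (ln 1.5)²) = 190.97, so 191.
- Participants in two groups: 191 / 0.30 = 636.7, so 637, or 319 per group.
- With drop-out: 319 / 0.90 = 354.4, so 355 per group, and 3 × 355 = 1065.

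The article states that "the total number of participants required is 1068 (ie, 356 participants per group"). The difference is 3 in 1068 (0.3%), so the figure reproduces and is not in dispute. First injuries expected: 1068 × 0.90 × 0.30 = 288.

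**2. End-of-intervention score.** Counted injuries fall inside the period that this rating closes. All of them (100%) precede it, with no assumption needed.

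**3. The 5-hour and 25-hour scores.** Weekly running hours, w, are not in the article. I assume 1 to 5 hours per week over 26 weeks, so total exposure is H = 26w. With 30% injured by H and a constant hazard per hour, the share of first injuries before hour h is

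(1 − 0.7^(h/H)) / 0.30.

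Example at 2 hours per week, h = 25: (1 − 0.7^(25/52)) / 0.30 = 0.53.

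| Hours/week (assumed) | Before 5 h | Before 25 h | Of 288, after 5 h | Of 288, after 25 h |
|---|---|---|---|---|
| 1 | 22% | 97% | 224 | 9 |
| 1.5 | 15% | 68% | 245 | 92 |
| 2 | 11% | 53% | 256 | 137 |
| 3 | 8% | 36% | 266 | 184 |
| 4 | 6% | 27% | 272 | 209 |
| 5 | 5% | 22% | 275 | 224 |

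**4. Sensitivity to hazard shape.** Replacing h/H by (h/H)^k, still over 1 to 5 hours per week:

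- k = 0.7 (early injuries more common): 98% to 35% before 25 hours, 35% to 12% before 5 hours.
- k = 1.3 (late injuries more common): 96% to 14% before 25 hours, 14% to 2% before 5 hours.

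**5. Who gives a 25-hour score.** The trigger is accumulated running, and the injury definition requires at least 7 days of restricted or stopped running. An injury before 25 hours therefore delays the rating or prevents it. Data collection ends participation for non-response, not for injury, and Study outcomes records return to full participation. An injured runner can thus resume, reach 25 hours and rate the shoe after the event. The 25-hour scores mix ratings given before injury with ratings given after it, and whether a score exists depends on the outcome.

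**6. Safeguards in the text.** The only analysis concerned with timing excludes runners injured in the first 2 weeks. Its stated purpose is the transition to the study shoe. It does not put perception before injury.

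**The case against.** The strongest reply is that this is a condensed article which gives mediation one sentence. The choice of score, landmarking and time-dependent coding are matters that a full analysis plan would settle. The later ratings have another use: the Introduction links them to shoe deterioration, and Objectives also relates perception to the shoe's actual cushioning, which needs no ordering against injury. Weekly hours are assumed, and 97% at 1 hour per week is close to automatic because 26 weeks then give only 26 hours. As a share of runners the figures are smaller: at 2 hours per week, 53% of a 30% incidence is about 16% of runners injured before 25 hours. Mediation comes last among the main analyses, and the perception objective is worded as an association.

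Much of this stands. A reader might infer that all three scores enter the mediation model; the article does not say so. A reader might also infer that the 25-hour score is confined to uninjured runners; it is not, because the trigger is hours run and injured runners can resume.

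What does not stand is that this is only an omitted detail. The article fixes both the clock (from inclusion) and the rating schedule (first at 5 hours). With those two choices, naming a score is not enough: even the 5-hour score used as a fixed variable has the ordering or selection problem. The Introduction's interest in perception changes as information on injury risk also points towards the later ratings.

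**Conclusion.** The point holds in this form: with risk time from inclusion, none of the three perception scores can be entered as a fixed mediator or predictor of first injury without reverse order or selection on staying uninjured. For the end score this is certain and total. For the 25-hour score, about 22% to 97% of first injuries come earlier, and for the 5-hour score about 5% to 22%, given 5 down to 1 hour per week, a constant hazard and 30% injured. The statement that most injuries precede the 25-hour rating is not supported in general: under a constant hazard it is about half or more at 2 hours per week or less, and about a quarter at 4 to 5 hours.

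The consequence is limited to the mediation analysis and secondary hypothesis 3. A reader might extend it to the shoe comparison or the sample size; neither uses perception, and 1068 reproduces. The 5-hour score precedes most injuries, so a sound analysis is possible with the data already planned.

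**What to change.** State the following, before injury outcomes are compared by shoe group:

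- **Mediation:** use the 5-hour score, with a landmark at 5 hours. Include runners who are still injury-free and at risk at 5 hours, and start risk time there.
- **Secondary hypothesis 3:** use the same 5-hour landmark. Alternatively, fit a cause-specific Cox model with the latest score recorded before each risk time as a time-dependent covariate. Fine-Gray is a poor fit for the second option, because runners stay in its risk set after a competing event, when their perception score may no longer be defined.
- **Later scores:** do not use the end score as a predictor or mediator of injury. Use 25-hour scores, or changes up to 25 hours, only for injuries after 25 hours.

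The cost is wording and programming, with no new data. Injuries before 5 hours leave both analyses, because no score exists before then: about 5% to 22% of events under a constant hazard, which keeps about 224 to 275 of the 288. If early injuries are more common, the loss could reach 35%. A 25-hour landmark would keep only about 9 to 224. Results would apply to runners uninjured at 5 hours, and the report should say so.

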## Discussion

Previous work has provided evidence that shoe cushioning effectively reduces injury risk in leisure-time runners.^17^ However, some important knowledge gaps remain to fill before designing the most effective running shoe for injury prevention. First, while the market is rapidly evolving towards greater cushioning, notably through the advent of super-critical foam technology since 2018, there is currently no data on the effect of these new materials (with greater cushioning properties) on injury risk. Second, running shoe design has evolved over the last decades, and runners are increasingly interested in shoe models with large stack height (and, consequently, greater cushioning) at the forepart of the shoe. While most literature has focused on cushioning (stiffness) at the rear part of the shoe to attenuate impact forces, force components unrelated to heel impact account for about half of the impact peak magnitude,^30^ which calls for more research on the possible effect of cushioning at the forepart of the shoe on injury risk.

